#### Cumulative effects.

To determine whether cumulative exposure to sexual strangulation is associated with longitudinal changes in neurological health, we will model repeated neurological outcomes collected every 6 months over 30 months using GLMMs (or linear mixed-effects models for continuous outcomes), a similar model structure to the acute aim. Each model will include a participant-specific random intercept to account for within-person correlation. Time will be modeled as a categorical variable (baseline, 6, 12, 18, 24, 30 months) for primary analyses to allow non-linear trajectories, and as a continuous variable in sensitivity analyses.

Primary longitudinal analysis will focus on: (1) overall group differences in trajectories between the strangulation and control groups via group × time interaction, and (2) within-group change over time (especially within the strangulation group) to identify when divergence from baseline emerges. Covariates will include age, prior concussion history, mental health diagnosis, and other clinically relevant time-varying factors assessed at each visit (e.g., mental health symptoms, substance use). For imaging outcomes, motion indices will be included.

To directly test the exposure-response hypotheses, we will incorporate time-varying measures of sexual strangulation exposure (e.g., frequency since last visit and cumulative frequency across follow-up; and, where available, intensity/duration and presence of alteration in consciousness) as predictors of neurological outcomes within the strangulation group. These models will estimate whether higher exposure is associated with worse neurological outcomes and whether this association strengthens over time by including exposure × time terms when appropriate.

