### Specific aims

Aim 1 To examine potential group differences at baseline in neurological health between the strangulation and control groups through comprehensive neurological measures.Hypotheses: (1a) Significant differences in brain activation patterns and neuronal connectivity, increases in blood biomarkers for astrogliosis, inflammation, and axonal microstructural injury, alteration in retinal integrity, and declines in cognitive, ocular-motor, and mental health function will be observed in the strangulation group compared to controls. (1b) We will explore potential mediating factors, including behavioral, history, and broader demographic factors, driving group differences in neurological health.Aim 2: To identify the acute neurological effects of sexual strangulation through the response profile of multimodal neuroimaging, blood biomarkers, cognitive and mental health assessments, and visual health assessments.Hypotheses: (2a) Within the strangulation group, significant alterations in brain activation patterns and neuronal connectivity, increases in blood biomarkers for astrogliosis, inflammation, and axonal microstructural injury, alteration in retinal integrity, and declines in cognitive, ocular-motor, and mental health function will be observed acutely (~24h) after being strangled during sex compared with baseline. (2b) The control group will have no worsening of neurological outcomes, resulting in a significant group difference at a post-acute time point. Also, individual cerebral hemodynamics via perfusion measure and fMRI activation patterns in risk and reward pathways will be explored in response to acute sexual strangulation events.Aim 3 To determine the associations between cumulative exposure to sexual strangulation and neural cellular, physiological, and functional integrities.Hypotheses: (3a) Frequent sexual strangulation will correlate with negative neurological outcomes, and this association will strengthen over time. (3b) The neurological impact of cumulative strangulation will be pronounced in blood biomarkers, indicative of astrogliosis, inflammation, and reduced axonal microstructural integrity, surface and subcortical morphology, neural activation patterns in the limbic regions, and cognitive function. (3c) Cumulative effects of sexual strangulation will also be captured through a series of mental health and visual health assessments. For those switching their sexual behavior (e.g., controls who report new onset of strangulation experiences), an exploration of how brain health changes as they initiate or cease engaging in sexual strangulation will be conducted.Aim 4: To examine longitudinal characteristics, perceptions, and experiences of sexual strangulation via semi-structured interviews.Semi-structured interviews in connection with each laboratory visit will address how one’s experiences with sexual strangulation change over time in terms of frequency, duration, methods of strangulation, consenting status, motivations, and associated symptoms. These data will not only play a crucial role in informing behavioral targets for educational guidelines and interventions, but also identify behavioral patterns and contextual factors that modify neurological outcomes. For example, our exploratory analysis will examine the role of alteration in consciousness (AIC), such as visual changes, disorientation, loss of consciousness, or dizziness) on neurological outcomes by comparing AIC and non-AIC subgroups.Exploratory Aim 5: To examine neurological implications of sexual strangulation among a pilot cohort of males.Since no neurological data related to sexual strangulation exist for males, pilot cohorts of males (n=20 per group) will be included to generate preliminary data and hypotheses for future research.Exploratory Aim 6: To explore various contextual and modulatory factors that are influencing neurological and psychological wellbeing over time in relation to sexual strangulation and non-strangulation related sex.Leveraging comprehensive assessments of participants’ demographics, prior sexual history, and contextual factors (e.g., menstrual cycle, birth control, sleep, substance/tobacco/alcohol use), we will explore how these factors contribute to individual responses to sexual strangulation and general sexual activities. This aim will include exploration of those who switch sexual behavior (e.g., stopping strangulation or control starting to engage in strangulation).

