#### Acute effects.

To examine the acute neurological effects of sexual strangulation, we will use a series of generalized linear mixed models (GLMMs) (or linear mixed-effects models for normally distributed outcomes) with each neurological variable as the dependent variable and visit type (baseline vs. post-acute) as the primary within-person predictor. Models will include a participant-specific random intercept to account for repeated measures. The primary interest will be the group (strangulation vs. control) × time (baseline vs. post-acute) interaction. Within-group time-effects will also be examined to assess group-specific time trends. Prespecified covariates will consider age, prior concussion history, and mental health diagnosis and/or mental health symptoms, as well as potentially adjusting for time since the most recent sexual event. We will also explore by including menstrual cycle phase and/or ovarian hormone levels as covariates. For neuroimaging outcomes, standard acquisition/quality covariates (e.g., motion indices) will be included. To address multiple comparisons across numerous endpoints, FDR will be applied within modality (biomarkers, imaging, ocular/retinal, cognition/mental health).

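### The six-visit longitudinal models name only a random intercept for within-person correlation; unless that correlation is the same at every lag, late-visit and cumulative-exposure standard errors will be too small and the month-6 standard error too large

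*Protocol article*

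**What the plan says.** The Cumulative effects section models outcomes measured every 6 months over 30 months with generalized linear or linear mixed models, described as "a similar model structure to the acute aim". On dependence between visits it says: "Each model will include a participant-specific random intercept to account for within-person correlation". The Acute effects section, which has two visits, uses the same device: "Models will include a participant-specific random intercept to account for repeated measures".

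On time it says: "Time will be modeled as a categorical variable (baseline, 6, 12, 18, 24, 30 months) for primary analyses to allow non-linear trajectories". A linear version of time has a supporting role: "and as a continuous variable in sensitivity analyses". It names no random slope, serial or unstructured residual covariance, or robust standard error, including where time becomes continuous.

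The primary longitudinal targets are the group × time interaction and "within-group change over time (especially within the strangulation group) to identify when divergence from baseline emerges". For exposure-response, within the strangulation group, "we will incorporate time-varying measures of sexual strangulation exposure (e.g., frequency since last visit and cumulative frequency across follow-up" and related measures enter as predictors.

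**The concern.** In a linear mixed model, a random intercept with independent residuals forces one correlation on every pair of visits and one common trajectory given the fixed effects. In a generalized model the same holds on the link scale. With two visits there is only one lag, so the assumption costs nothing. With six visits over 30 months it is a real restriction.

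The model estimates one pooled within-person variance and uses it for every visit contrast. If adjacent visits are more alike than distant ones, that pooled value is too large for month 6 minus baseline and too small for month 30 minus baseline. A predictor that accumulates over follow-up behaves like a person-specific slope, so its standard error is also too small.

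These are the quantities on which Aim 3 rests. Early divergence would be under-detected, and late divergence and exposure-response would be declared too often. The apparent onset could therefore move later purely because of the covariance assumption.

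**Working it through.** **The plan's own figure.** The documents state no figure for the correlation structure. The nearest is in Sample size: power above 80% with 100 females per group, d = 0.50, alpha 0.01 and 20% loss. With 80 per group left, a plain two-sample comparison gives 72.1% two-sided or 79.8% one-sided. The mean of six equally correlated visits, with variance factor (1 + 5ρ)/6, gives 81% at ρ = 0.8 and 99% at ρ = 0.3. The figure is thus reachable by a standard variant, but it does not reveal which between-visit correlation was assumed.

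**Inputs.** From the article: six visits (0 to 30 months), random intercept, 100 per group less 20% = 80. Assumed, because not given: constant correlation 0.7; AR(1) correlation 0.70–0.95 per 6 months; a stable half plus AR(1) 0.6–0.8; or a random intercept (variance 0.7) with noise 0.3 and a between-person SD of 30-month change of 0.2–0.7 baseline SD.

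**Formulas** (balanced, complete data). Let V be the true 6 × 6 covariance and P = I − J/6, with J the all-ones matrix.
- Pooled within-person variance used by the model: s² = tr(PV)/5.
- Model variance of visit k minus baseline, per person: 2s². True variance: V₀₀ + Vₖₖ − 2V₀ₖ.
- Ratio r = model SE / true SE. Actual error at nominal 5%: 2[1 − Φ(1.96 r)].

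**Worked case 1, AR(1) 0.8.**
- The elements of V sum to 6 + 2(5×0.8 + 4×0.64 + 3×0.512 + 2×0.4096 + 0.32768) = 24.486.
- tr(PV) = 6 − 24.486/6 = 1.919, so s² = 0.3838 and the model variance is 0.7676.
- Month 30: true variance 2(1 − 0.32768) = 1.3446; r = √(0.7676/1.3446) = 0.76; error 13.9%.
- Month 6: true variance 2(1 − 0.8) = 0.40; r = √(0.7676/0.40) = 1.39; error 0.7%.

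**Worked case 2, random slope SD 0.5.**
- Visit times scaled 0 to 1 have a sum of squared deviations of 0.7. So tr(PV) = 5×0.3 + 0.25×0.7 = 1.675, s² = 0.335 and the model variance is 0.67.
- Month 30: true variance 0.6 + 0.25 = 0.85; r = 0.89; error 8.2%.
- Month 6: true variance 0.6 + 0.25×0.04 = 0.61; r = 1.05; error 4.0%.

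**All targets, actual error at nominal 5%** (r in brackets). The joint test used 20,000 draws. The cumulative-exposure column is 2,000 simulated null trials per row: 80 exposed participants, gamma-distributed individual rates, REML random-intercept fit with categorical time.

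| True structure | Month 6 | Month 30 | Linear slope | Joint 5-df | Cumulative exposure |
|---|---|---|---|---|---|
| Constant 0.7 | 5.0% (1.00) | 5.0% (1.00) | 5.0% | 5.0% | 5.0% (1.02) |
| AR(1) 0.90 | 0.4% (1.45) | 15.9% (0.72) | 25.0% | 8.6% | 24.5% (0.59) |
| AR(1) 0.80 | 0.7% (1.39) | 13.9% (0.76) | 22.7% | 8.0% | 20.8% (0.64) |
| AR(1) 0.70 | 1.0% (1.32) | 12.0% (0.79) | 20.3% | 7.3% | 16.7% (0.70) |
| Stable half + AR(1) 0.8 | 0.7% (1.39) | 13.9% (0.76) | 22.7% | 8.0% | 21.5% (0.63) |
| Slope SD 0.3 | 4.6% (1.02) | 6.2% (0.95) | 6.9% | 5.1% | 6.1% (0.96) |
| Slope SD 0.5 | 4.0% (1.05) | 8.2% (0.89) | 10.0% | 5.3% | 11.7% (0.80) |
| Slope SD 0.7 | 3.3% (1.09) | 10.7% (0.82) | 13.8% | 5.7% | 15.3% (0.73) |

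At the extremes of the assumed grid, month-30 error is 5.5% (slope SD 0.2) and 17.0% (AR(1) 0.95). At nominal 1%, over the range from slope SD 0.3 to AR(1) 0.90, month-30 error is 1.4–6.4% and cumulative-exposure error 1.4–12.8%. Uncorrected participant-clustered robust SEs on the same exposure fits gave 5.9–8.0% at nominal 5%.

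**The case against.** - **The text does not exclude more.** It says that models will include a random intercept, and the article is condensed. A reader might infer that a random slope or residual covariance is ruled out; the wording does not go that far, and a full analysis plan may add one. What remains is that the article gives the random intercept as its means of handling within-person correlation and takes it over from a two-visit model. Followed as written, that is a stated choice.
- **The harm is conditional.** A reader might infer that the error bars are too narrow as a matter of fact. The documents give no correlation that would show it. Under constant correlation there is no distortion, and with small slope variance it is slight. This stands.
- **The overall group × time test is little affected**, and the continuous-time slope belongs only to sensitivity analyses. Both stand. They leave late single-visit contrasts and the cumulative-exposure coefficient as the main casualties.
- **Hypothesis 3a** ("Frequent sexual strangulation will correlate with negative neurological outcomes, and this association will strengthen over time") might be read as the plan's own admission that slopes vary. It is not. It describes a fixed effect, which the plan models through time-varying exposure and exposure × time terms. Under the null of no exposure effect it generates no residual slope variance, so that variance has to be assumed separately.
- **The calculation idealizes the data.** Recruitment may run to March 2029 and data collection ends in May 2030, 14 months later, so late enrollees cannot reach month 30. Post-switch data also leave the primary analyses. Neither is modelled, so the sizes are illustrative and the direction is the firmer result.

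**Conclusion.** The point holds as a conditional defect in a stated modelling rule. Unless within-person correlation is the same at every lag, the rule gives standard errors that are too small for late contrasts, cumulative exposure and the sensitivity slope, and too large at month 6. Every non-constant structure tested showed this pattern. Between slope SD 0.3 and AR(1) 0.90, actual error at nominal 5% is about 6–16% at month 30, about 6–25% for cumulative exposure and about 7–25% for the linear slope, against 0.4–4.6% at month 6. The joint test stays at about 5–9%. These figures assume complete data, 80 per group and correlations that the documents do not supply. They do not show that the study's intervals will be wrong by any particular amount, or that the overall group × time test is unsound. Severity: should-fix.

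**What to change.** In Statistical analyses, Cumulative effects:
- For categorical-time models of continuous outcomes, specify an unstructured residual covariance across the six visits, with a random intercept plus a serial (AR) structure as the convergence fallback.
- For the continuous-time models, the cumulative-exposure models and the GLMMs, specify a random intercept plus a random slope for time, with serial residual correlation where needed.
- Use Kenward-Roger or Satterthwaite degrees of freedom, or participant-clustered robust SEs with a small-sample correction, since the uncorrected version remained above nominal in the check.
- Keep the random intercept for the two-visit acute analysis.

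The cost is analysis wording only: some intervals will widen and a convergence fallback has to be prespecified. Design, visits and sample size stay as they are, and the change can be made before 30-month data exist.

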
### Outcome measures

Our outcomes (Table 1) will be assessed by comparing group differences, specifically group (strangulation vs control) x time interaction, as well as within-group time-course changes in outcomes.

**Table 1 pone.0344672.t001:** Outcome measures.

Outcome Measure	Type	Test/Task and Description
Blood biomarkers	Primary outcome	The primary outcome analyses will be comparing group differences (group x time interactions) and within-group time-course changes in blood biomarkers, specifically NF-L, tau, GFAP, UCH-L1, p-tau 181, p-tau 217, and S100-beta. Additional panel of inflammatory cytokines and chemokines will be explored: IL-1b,1a,2,6,8,10,17; CCL2,3,5; and VCAM, PCAM, angiopoietin, and neureglin.
Structural neuroimaging	Primary outcome	Cortical and subcortical morphometry analyses will yield macro-structural variables (thickness, volume, gyrification, sulcal depth) across the brain. For analysis of microstructural integrity, DTI and NODDI measures will be used to derive MD, axial and radial diffusivity, fractional anisotropy, NDI, ODI, and ICVF.
fMRI imaging	Primary outcome	Resting-state connectivity will be examined throughout the whole brain and specific seeded regions including the DLPFC, angular gyrus, and cingulate gyrus. Task-based fMRI using the BART will assess neural activity (inhibition and excitation) during risk-taking behaviors in the risk-reward circuitry.
Clinical assessments	Primary outcome	Cognitive function will be measured using the NIH Toolbox Cognition Battery, which examines 5 cognitive domains (executive function, episodic memory, language, working memory, and processing speed). Oculomotor function will be tested by NPC. The NPC measures will be repeated twice, and the mean NPC (in centimeters) will be used for analyses. Mental health-related symptoms will also be treated as primary outcomes, which include depression, stress, anxiety, ADHD, personality traits, and sleep.

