### Statistical analyses

#### Baseline group analysis.

To test whether neurological outcomes differ at baseline between the strangulation and control groups, we will use multivariable regression models with each baseline neurological outcome as the dependent variable and group (strangulation vs control) as the primary independent variable. For continuous outcomes (e.g., biomarker concentrations, imaging metrics, cognitive scores, NPC distance, OCT measures), we will use linear regression (or generalized linear models with appropriate functions if distributional assumptions are not met). For binary outcomes (e.g., presence/absence of symptoms or threshold-defined impairment), we will use logistic regression. Models will adjust for prespecified baseline covariates that are clinically relevant and/or imbalanced between groups, including age, BMI, prior concussion history, and baseline mental health symptoms. Because baseline neural health may be influenced by contextual factors, we will additionally consider time since last sexual event, substance use, sleep, and ovarian hormone levels/menstrual cycle phase as covariates when relevant to specific outcomes. For imaging outcomes, scanner-related and acquisition covariates (e.g., motion indices) will be included as standard quality-control adjustments. We will control for multiple comparisons using a false discovery rate (FDR) approach within each modality (biomarkers, imaging, ocular/retinal, cognition, mental health). As a complementary approach that leverages correlation among outcomes, we will conduct multivariate testing within domains (e.g., principal-component-based composite scores) to evaluate whether a domain shows an overall baseline difference by group prior to interpreting individual endpoints. Where appropriate, we also may consider exploratory mediation and explanatory models to help explain baseline group differences. We will use mediation analyses to estimate indirect effects while adjusting for confounders.

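### Mental-health symptoms are primary outcomes expected to respond to strangulation, yet the primary longitudinal models adjust for them at each visit and the Aim 1 models adjust for them at baseline

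*Protocol article*

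**What the plan says.** **Symptoms as outcomes.** Table 1 (Outcome measures) states: "Mental health-related symptoms will also be treated as primary outcomes, which include depression, stress, anxiety, ADHD, personality traits, and sleep". Under Specific aims, hypothesis 1a predicts "declines in cognitive, ocular-motor, and mental health function will be observed in the strangulation group compared to controls". Hypothesis 2a predicts the same kind of decline acutely, and hypothesis 3c expects cumulative effects to appear in mental-health assessments. The Discussion gives the direction as strangulation influencing mental-health functioning.

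**Symptoms as covariates.**
- Cumulative effects: the covariates of the primary longitudinal models include age, prior concussion, diagnosis and "other clinically relevant time-varying factors assessed at each visit (e.g., mental health symptoms, substance use". Symptoms are given as an example, but in a list of what the models will contain.
- Baseline group analysis: the Aim 1 regressions will adjust for "prespecified baseline covariates that are clinically relevant and/or imbalanced between groups, including age, BMI, prior concussion history, and baseline mental health symptoms".
- Acute effects: the wording is softer: "Prespecified covariates will consider age, prior concussion history, and mental health diagnosis and/or mental health symptoms".

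**No exemption.** Mental health is one of the families for false-discovery-rate control in the Baseline group analysis, and is grouped with cognition in Acute effects. The mental-health outcomes are therefore analysed in these models. Baseline group analysis limits its contextual covariates, sleep among them, to outcomes for which they are relevant. It sets no such limit on mental-health symptoms. No section names a primary model without symptoms or says that a direct effect is the target. Mediation is mentioned only as exploratory work on baseline differences.

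**The concern.** A variable that the exposure is expected to change should not be held fixed in the model that estimates the total effect of that exposure. There are three consequences.

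1. **Mental-health outcomes.** Adjusting a depression score for itself is degenerate. Adjusting it for anxiety or stress at the same visit removes much of what the two scales share, including a shared response to strangulation.
2. **Other outcomes.** Same-visit symptoms lie on a possible pathway from strangulation to biomarkers, imaging and cognition. Conditioning on them leaves a partly direct effect and may open collider paths. Aim 3 asks for the association with cumulative exposure, not for the part that bypasses mental health.
3. **Aim 1.** Participants states that the strangulation group must have been strangled at least four times in the month before enrolment. Their baseline symptoms are therefore already post-exposure, and the adjustment can remove part of the baseline difference under test.

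At stake is a null or weakened result on a primary outcome that is produced by the covariate list.

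**Working it through.** **Inputs from the article (Sample size).** d = 0.50, alpha 0.01 (taken as two-sided, since sidedness is not stated), 100 females per group, up to 20% dropout or switching, and claimed power above 80%.

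**Assumed inputs, because the article gives none.** dM is the group difference in symptoms in SD units, range 0 to 0.8. b is the within-group slope of outcome on symptoms in SD units, range 0.2 to 0.5. Within-person correlation is 0.5 in the simulation.

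**Step 1: the plan's own figure.** Power = Φ(d/√(2/n) − 2.576).
- n = 100: 0.50/0.1414 = 3.536, so Φ(0.960) = 83.1%.
- n = 80 (after 20% loss): 0.50/0.1581 = 3.162, so Φ(0.586) = 72.1%.

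A repeated-measures gain can bring 80 per group above 80% (for example 83.1% for a change score with correlation 0.6). The article states no correlation, so its figure is neither confirmed nor refuted. The point here does not depend on it.

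**Step 2: effect left after adjusting for symptoms.** Adjusted coefficient = d − b × dM. SE = √(1 − b²) × √(2/n) × √(1 + dM²/4). With d = 0.50 and n = 100:

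| dM | b | Adjusted coefficient | Share lost | Power (83.1% unadjusted) |
|---|---|---|---|---|
| 0.3 | 0.2 | 0.50 − 0.06 = 0.44 | 12% | 71% |
| 0.5 | 0.3 | 0.50 − 0.15 = 0.35 | 30% | 48% |
| 0.5 | 0.5 | 0.50 − 0.25 = 0.25 | 50% | 28% |
| 0.8 | 0.5 | 0.50 − 0.40 = 0.10 | 80% | 4% |
| 0 | any | 0.50 | 0% | no loss |

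**Step 3: does this carry over to group-by-time?** A six-visit random-intercept model was simulated with time categorical, 80 per group and 2,000 replicates. The true group-by-time difference at 30 months was 0.50. Mean estimates:

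| dM at 30 months | b | No symptom covariate | Baseline symptoms only | Same-visit symptoms |
|---|---|---|---|---|
| 0.5 | 0.3 | 0.50 | 0.50 | 0.35 |
| 0.5 | 0.5 | 0.50 | 0.50 | 0.25 |
| 0.8 | 0.5 | 0.50 | 0.50 | 0.10 |
| 0 | 0.5 | 0.50 | 0.50 | 0.50 |

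The time-varying covariate removes b × dM, as in step 2. A baseline-only covariate enters as a constant per participant and cancels from the change over time.

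**Step 4: one symptom scale adjusted for another.** Suppose strangulation shifts both scales by 0.50 and their within-group correlation is r (assumed). The effect in residual SD units is (0.50 − 0.50r)/√(1 − r²).
- r = 0.3: 0.35/0.954 = 0.37
- r = 0.6: 0.20/0.800 = 0.25
- r = 0.7: 0.15/0.714 = 0.21

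The simulation with slope 0.7 and dM 0.5 agrees: the 30-month coefficient falls from 0.50 to 0.15.

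**The case against.** The strongest reply is confounding. This is a self-selected observational cohort. The Introduction names the difficulty of separating pre-existing differences from strangulation effects, and Participants keeps common psychiatric conditions in the sample on the promise that they will be handled analytically. Mental-health covariates carry out that promise. This stands. It rules out dropping all mental-health adjustment, and it supports keeping a diagnosis history that predates exposure; screening collects current and past diagnoses. It does not justify same-visit symptoms in a primary total-effect model, because those are measured after exposure and are predicted to respond to it.

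A second reply is that no sentence says a symptom scale will be adjusted for itself, and that outcome-specific covariate lists usually sit in an analysis plan. It is true that the article does not spell this out for each outcome. But it does state a general covariate rule, applies it to models that include the mental-health outcomes, and gives no exception. Following the rule as written produces the problem.

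Three stronger readings are tempting and are not supported:
- That the strangulation effect as a whole is adjusted away. Only the part running through symptoms is removed; near-total loss needs near-full mediation, or a mental-health outcome adjusted for itself or a close proxy.
- That baseline symptom adjustment damages all three analyses. It can remove effect in the cross-sectional Aim 1 model, but step 3 shows group-by-time unchanged. The acute models have group-by-time as their primary interest, and there symptoms are only to be considered.
- That covariates will be picked by observed imbalance. The Baseline group analysis wording is loose on this, but it calls the covariates prespecified and names them.

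**Conclusion.** The conflict is in the text. One construct is a primary outcome predicted to respond to strangulation and also a covariate in the primary longitudinal models and in Aim 1. The problem is clearest for same-visit symptoms in Cumulative effects, and for any mental-health outcome adjusted for mental-health symptoms. It also holds for the Aim 1 regressions, where the same adjustment may remove confounding as well as effect.

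The size cannot be read from the article. Under the assumed ranges for dM and b, 12% to 80% of a d = 0.50 effect is lost, and none if strangulation does not change symptoms. That last case would contradict hypotheses 1a, 2a and 3c. The calculations treat symptoms as a mediator only. Where symptoms also confound, the adjusted estimate may be closer to the truth in part, so both estimates should be shown with their roles fixed in advance.

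**What to change.** 1. Do not adjust any mental-health outcome, including sleep, for concurrent or baseline symptom scores, other than its own baseline value as a repeated measure.
2. For the other outcomes, leave same-visit symptom scores out of the primary longitudinal models. Keep adjustment for factors that plausibly precede exposure: age, prior concussion, childhood adversity (already collected at baseline), and mental-health diagnosis history where onset predates exposure.
3. For Aim 1, report estimates with and without baseline symptoms. Label the symptom-adjusted models, at baseline and longitudinally, as sensitivity or mediation analyses. If symptoms are thought to be both confounder and mediator over time, a method built for that, such as a marginal structural model, belongs among them.

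The cost is a change of wording and some extra models to report, with no new data. The downside is that some confounding by pre-existing mental health may remain in the primary estimate, and the sensitivity models are there to show it. The article expects recruitment from late February 2026 and primary analyses finished by May 2031, so the change can be made before outcome data are seen.
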